### 3. STUDY DESIGN

The proposed study will be a double-blind, randomized placebo-controlled trial, to evaluate the effect of a potato-pectin fibre mixture on gut, metabolic, immune and brain health by optimizing saccharolytic and proteolytic fermentation. Individuals aged 30-75 years with overweight or obesity ( $\text{BMI} \geq 28 \text{ kg/m}^2 < 40 \text{ kg/m}^2$ ) and impaired fasting glucose (defined as fasting glucose 5.6-6.9 mmol/l or HbA1c 42-47 mmol/mol) or insulin resistance ( $\text{HOMA-IR} > 1.85$ ) will be included in the study.

All visits regarding this study will take place at the facilities of the department of human biology or the Metabolism Research Unit Maastricht of Maastricht University, or at the clinical facilities of Maastricht University Medical Center+.

After the application of an individual via (e-)mail or phone (see [Chapter 4](#) for recruitment), the researcher will contact the potential participant by email or phone to provide additional information regarding the study, answer questions and determine possible eligibility, after which a week of consideration will be given. After a week, the potential participant will be contacted again and, if they are still interested in participating, a screening visit will be planned.

The first visit to our facilities will consist of the following components:

- Checking an individual's wellbeing, medical history and determining eligibility and safety of participation.
- Signing informed consent
- Measuring vital parameters and body measurements (body weight, length, waist-to-hip ratio, systolic and diastolic blood pressure)
- Taking blood samples to determine eligibility based on specific inclusion criteria (20ml to determine glucose, insulin, ALAT, creatinine, HbA1c)

The participant will visit our facilities after a >10h overnight fasted state.

All eligible participants will be equally randomized over the two arms (potato-pectin fibre mixture vs placebo) with stratification for age, sex and HbA1c (see [Chapter 8.2](#)). The entire trial period after screening and randomization will take 13 weeks, which will be explained in more detail below.

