## **8. METHODS**

### **8.1 Study parameters/endpoints**

#### **8.1.1 Main study parameter/endpoint**

The main endpoint is the difference in change in peripheral muscle insulin between intervention and control group, measured by hyperinsulinemic-euglycemic clamp.

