### **8.2 Randomisation, blinding and treatment allocation**

Participants will be randomized to the intervention or placebo group using a validated variable block randomization using Qminim. Furthermore, minimization will be used to ensure group comparability. Factors included for minimization are age, sex and BMI.(40) Initially, CASTOR

EDC would be used for randomization and stratification for this study. After the change from stratification to minimization, however, CASTOR cannot be used since it has no minimization option. Therefore, Qminim will be used, with which there is extensive experience within our research group.

Randomization and preparing and distribution of the, for participant and investigator, unrecognizable dietary supplement (either a potato-pectin fibre mixture or placebo) will be carried out by an independent researcher. This ensures that only the independent researcher knows which subject received which supplement, while both the participant and original investigator remain blinded to the treatment. In case of emergency, the independent investigator can debind the participant(s).

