**8.3.10 Two-step hyperinsulinemic-euglycemic clamp**

To assess whole-body and tissue-specific insulin sensitivity, we will be performing a two-step hyperinsulinemic-euglycemic clamp, which is the gold standard to determine insulin sensitivity. The clamp will be performed on CID 2 and 4 and will take place after a >12h overnight fasting period and a standardized meal the evening before. Before starting the procedure, an intravenous canula will be inserted in an antecubital vein to provide intravenous access for insulin and glucose suppletion. Another intravenous canula will be inserted on the dorsal side of the contralateral hand to ensure intravenous access for blood sampling.

At  $t = 0$  minutes, a fasting blood sample (10ml) will be drawn, followed by infusion of a primed 6,6-H2-glucose tracer at 0.04mg/kg/min, which will be used to calculate endogenous glucose production (EGP), glucose appearance (Ra) and glucose disposal. Therefore, blood samples (6ml) will be drawn at  $t=90$ , 105 and 120 min. At  $t = 120$ min, insulin will be infused at a low,

constant rate of 10 mU/m^2/min for 3 hours to allow determination of hepatic glucose production. After 3 hours ( $t = 300\text{min}$ ), insulin infusion will be increased to 40 mU/m^2/min to inhibit EGP for 2.5 hours, providing insight in muscle insulin sensitivity. During insulin suppletion, plasma glucose levels will be measured every 5 minutes (1ml), upon which glucose (20% glucose solution) will be infused at 10-30ml/h to ensure a constant plasma glucose level of 4.8-5.2 mmol/l during the clamp. Afterwards, the total amount of infused glucose can be used to determine insulin sensitivity. Additional blood samples (6ml) will be drawn at  $t = 180, 240, 270, 285, 400, 420, 435$  and 450 minutes.

At  $t = 450\text{min}$ , insulin infusion will be terminated and glucose infusion will be slowly reduced to zero to ensure a safe normalisation of glucose homeostasis. Additional dietary supplements will be provided (sandwiches, drinks) to prevent a hypoglycemic state.

During the clamp, an indirect calorimetry will be performed, which will be described below.

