## 10. STATISTICAL ANALYSIS

The statistical analyses will be carried out by the investigator using SPSS software. Regarding descriptive statistics, numerical variables will be reported as mean  $\pm$ SD. Categorical variables will be reported as numbers and percentages. To test for normality of the data, Histogram and Kolmogorov-Smirnov test will be used. In case, of non-parametric data, the data will be transformed using natural logarithm. In general, a p-value  $<0.05$  will be considered statistically significant using two-tailed tests. In case of missing data, we will perform multiple imputation (MI) to estimate the missing value. MI is the process of replacing each missing data point with a set of  $m > 1$  plausible values to generate  $m$  complete data sets. Multiple imputation has been shown to produce valid statistical inference that reflects the uncertainty associated with the estimation of the missing data.

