### 10.1 Primary study parameter(s)

We will be comparing the intervention group versus the placebo group regarding the change in insulin sensitivity as measured by the two-step hyperinsulinemic-euglycemic clamp. Changes in glucose disposal rate and infused glucose concentrations before and after the 12 week intervention period are our primary study parameters and will be analysed and compared between the two groups. Data from both groups will be analysed using a linear mixed model to include repeated measures. An intention-to-treat and per-protocol analysis will be conducted. Intervention and study period will be set as fixed factors, participants will be set as random factor. Age and sex will be added as covariates in the analysis.

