### 10.2 Secondary study parameter(s)

All additional gathered data will be analysed to answer our secondary objectives ([Chapter 2](#)), using the same methods as described above. We will be using linear mixed model for repeated measures, t-tests and regression models, depending on the specific data and requirements to assess each secondary objective. Anthropometrics, energy balance, substrate metabolism, urine and blood values will be presented as mean  $\pm$  standard error.

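### Read as main effects, the age and sex covariates drop out of the primary difference in change, so the stated adjustment buys no precision

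*Protocol*

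**What the plan says.** Protocol section 8.1.1 defines the endpoint: "The main endpoint is the difference in change in peripheral muscle insulin between intervention and control group". Section 8.3.10 fixes two measurements per person: "The clamp will be performed on CID 2 and 4".

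Section 10.1 gives the model as a linear mixed model: "Intervention and study period will be set as fixed factors, participants will be set as random factor". It then states: "Age and sex will be added as covariates in the analysis". It names no intervention-by-period term, no covariate-by-period term and no baseline covariate.

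On allocation, section 8.2 says: "Factors included for minimization are age, sex and BMI". On missing values, section 10 says: "In case of missing data, we will perform multiple imputation (MI) to estimate the missing value". Section 10.2 analyses the secondary endpoints "using the same methods as described above", choosing among mixed models, t-tests and regression according to the data.

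**The concern.** Balancing the arms on age and sex and then adjusting for them is sound practice. Minimisation makes the arms alike on these factors, and the adjustment removes from the error term the variation that they explain. That second half works only if the covariates can reach the contrast being tested.

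Here the contrast is a difference in within-person changes. A covariate that takes the same value at both visits shifts both measurements equally and disappears when one is subtracted from the other. The protocol evidently intends an adjustment. As the sentence is ordinarily read, the primary contrast does not receive it. If age and sex predict how much insulin sensitivity changes, the interval is wider than it need be, the test runs somewhat below its nominal 5%, and some power is lost. Any secondary endpoint analysed with the same model inherits this.

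**Working it through.** **Inputs.** From section 4.4: post-measurement SD 3.95, pre-post correlation 0.73, difference 2.86 µmol/kg/min, 22 per arm, 20% dropout, α 0.05. Section 10 makes tests two-tailed. Completers per arm: 22 × 0.8 = 17.6, taken as 18.

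**The plan's own SD.** √(1 − 0.73²) × 3.95 = 2.70, as stated. This is the SD of the post value after adjustment for baseline. A difference in change without baseline adjustment carries a different SD. Assuming equal pre and post SDs, it is √(2 × (1 − 0.73)) × 3.95 = 2.90.

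**The cancellation.** For person *i* in period *t* (0 or 1), with main-effect covariates:

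y_it = μ + α·arm_i + π·t + δ·(arm_i × t) + β₁·age_i + β₂·sex_i + u_i + e_it

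Subtracting the two periods gives:

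y_i1 − y_i0 = π + δ·arm_i + (e_i1 − e_i0)

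The age, sex and participant terms have all gone. δ is the section 8.1.1 endpoint, and its estimate and error do not involve β₁ or β₂. Multiple imputation makes each analysed data set complete, so the same holds in each.

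**Numerical check.** One simulated trial (22 per arm, SD 3.95, r 0.73, with assumed effects of age and sex on both level and change), random-intercept REML fit:

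| Model | Estimate of δ | SE |
|---|---|---|
| Intervention × period, no covariates | 2.9897 | 1.1143 |
| The same + age + sex | 2.9897 | 1.1143 |
| The same + age × period + sex × period | 3.3499 | 1.0720 |

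Main effects change nothing to four decimals; the by-period terms change both columns. This is a single data set with simple allocation, so the movement in the estimate reflects chance imbalance on age and sex and is not evidence of bias.

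**Size of the loss.** Let R² be the share of the variance of change that age and sex explain. The protocol gives no value, so the range is an assumption. An effective adjustment reduces the SD to 2.90 × √(1 − R²). Power is from the noncentral t with 18 per arm and noncentrality 2.86 / (SD × √(2/18)). The last column is the true type I error of the unadjusted test, 2 × (1 − Φ(1.96 / √(1 − R²))), if the arms are perfectly balanced on both factors.

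| Assumed R² | SD of change, adjusted | Power as written | Power, effective adjustment | Type I error as written |
|---|---|---|---|---|
| 0 | 2.90 | 82% | 82% | 5.0% |
| 5% | 2.83 | 82% | 84% | 4.4% |
| 10% | 2.75 | 82% | 86% | 3.9% |
| 20% | 2.60 | 82% | 89% | 2.8% |

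Charging two degrees of freedom for the extra terms lowers power by about 0.1 percentage points (81.9% becomes 81.8% at R² = 0). With 17.6 rather than 18 completers, power as written is 81%.

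**The case against.** **The protocol does not say main effects only.** This is correct. It says that age and sex are added as covariates, and covariate-by-period terms are detail that a statistical analysis plan could supply. The point therefore rests on the ordinary reading of the sentence, not on an explicit exclusion.

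**The cancellation needs an intervention-by-period term that section 10.1 does not name.** Also correct, and under other models age and sex do matter. In the same simulated trial, with only the listed terms and no interaction, adding them moved the intervention coefficient from 1.54 (SE 1.26) to 2.18 (SE 1.01). With a common baseline mean for the two arms, the effect moved from 3.00 (SE 1.02) to 3.31 (SE 0.98). But the first coefficient averages the arms' difference over both periods and is not the section 8.1.1 endpoint. The second needs a baseline constraint that section 10.1 does not mention. Neither rescues the sentence for the endpoint as defined.

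**The sample size points to a baseline-adjusted analysis.** The SD of 2.70 in section 4.4 belongs to such an analysis, and there age and sex as plain covariates would work. This is the best argument that the intention was sound. It supports the second remedy below, but section 10.1 does not describe that analysis.

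**The harm is small and rests on an assumed R².** This stands. At R² = 0 nothing is gained, and the planned 80% power is met without any change. The type I figures assume perfect balance. Minimisation in 44 people will not achieve that, so they mark the largest conservatism.

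**A reader might infer** that the primary result is biased or the trial underpowered, or that every secondary endpoint is affected. The documents support none of these. Randomisation keeps the contrast unbiased, power is about 81% to 82% as written, and section 10.2 also allows t-tests and regression, with section 4.4 calling the secondary outcomes exploratory.

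**Conclusion.** The point holds as a matter of precision. For a difference in change over two clamps, with complete or imputed data and the covariates read as main effects, the stated adjustment for age and sex has exactly no effect on the primary contrast. Validity is not threatened.

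The gain forgone runs from nothing at R² = 0 to about 7 percentage points of power at R² = 20% (82% to 89%). These figures assume 18 completers per arm and equal pre and post SDs. This is a cheap improvement worth making, not a defect that undermines the trial.

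**What to change.** In section 10.1, choose one of two forms and state it:

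- Keep the two-period mixed model, name intervention-by-period as the primary contrast, and enter age × period, sex × period and the third minimisation factor × period.
- Make the primary analysis the post value adjusted for baseline, with age, sex and the third minimisation factor as covariates. This also matches the SD of 2.70 used for the sample size.

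The third factor is BMI in section 8.2, whereas section 3 still reads "with stratification for age, sex and HbA1c". Reconcile the two before it is written into the model. Adding BMI as one more main effect to the model in section 10.1 would not help, because it would cancel in the same way.

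Use the chosen form for those secondary endpoints that are analysed with this mixed model. The cost is a sentence or two of text and two or three degrees of freedom; no new data are needed.

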### 10.2 Secondary study parameter(s)

All additional gathered data will be analysed to answer our secondary objectives ([Chapter 2](#)), using the same methods as described above. We will be using linear mixed model for repeated measures, t-tests and regression models, depending on the specific data and requirements to assess each secondary objective. Anthropometrics, energy balance, substrate metabolism, urine and blood values will be presented as mean  $\pm$  standard error.

#### *Microbial composition*

The microbiota composition based on 16S rRNA analysis or metagenome analysis will be determined from DNA isolated from faecal samples. Diversity of the microbiota will be calculated by i.e. Shannon-index. Moreover, to determine the effects of the intervention on for instance single bacterial groups, linear mixed model analysis will be conducted using an unstructured covariance structure for repeated measures.

### 10.3 Other study parameters

Not applicable

**10.4 Interim analysis (if applicable)**

Not applicable

## **11. ETHICAL CONSIDERATIONS**

### **11.1 Regulation statement**

The study has to be approved by the Medical Ethical Committee of the Maastricht University and academic hospital (medisch-ethische toetsingscommissie azM/UM, METC azM/UM). The study will be conducted according to the Declaration of Helsinki (64th WMA General Assembly, Fortaleza, Brazil, October 2013) and in accordance with the Medical Research Involving Human Subjects Act (WMO). The general principles of informed consent, ethics review and data management will be in line with GCP.

### **11.2 Recruitment and consent**

Recruitment will take place via advertisements in local newspapers and social media, as well as posters hung around the Maastricht University and Maastricht University Medical Centre+. Furthermore, websites related to recruitment of participants for scientific trials will be used to attract participants. Additionally, if participants from other trials that were carried out within our research group have agreed to be contacted for future research will be contacted via email to ask request participation.

If a person is interested in participating, he/she can contact the investigators via email or telephone using the via advertisements provided contact details to express their interest. Eventually, the investigators will contact the possible participants via telephone to provide additional information, answer questions and discuss inclusion and exclusion criteria to enable the interested persons to determine whether they can and want to participate in this trial. Furthermore, the participant information documents will be provided via (e-)mail. Afterwards, participants will be given one week of contemplation before the investigators recontact the interested persons to answer questions, provide additional information if necessary and assess whether the person still wants to participate. If a person expresses continued interest, a screening visit will be planned to assess eligibility. During this visit, the investigators check whether all provided information is understood, answer arisen questions and provide additional information if necessary. If willingness to participate persists during this visit, the informed consent form will be signed in presence of the investigator. Afterwards, the screening will take place (see [chapter 8.3.1](#)). People that don't meet the inclusion or meet any of the exclusion criteria will not be included in the randomization and will be considered drop-outs.

### **11.3 Objection by minors or incapacitated subjects (if applicable)**

Not applicable

### 11.4 Benefits and risks assessment, group relatedness

In general, obesity and its related diseases bring a high burden to a patients wellbeing and quality of life. Furthermore, these diseases are one of the leading causes of death worldwide, have a high socio-economic impact on society, and thus increase health care costs. By evaluating possible strategies to improve metabolic, gut and brain health, we want to attribute to a healthier lifestyle, a decrease in obesity and obesity-related diseases and in the socioeconomic impact of said diseases.

By testing the pre-established, possibly beneficial dietary component, we will gain insight in specific metabolic pathways, analyse interactions between food, gut and brain, and find potential ways to steer the human digestive system to provide beneficial substrates and reduce detrimental by-products. Along with the purpose of finding fundamental evidence to support further preventative or therapeutic interventions and studies, participants might benefit individually from the intervention in terms of small short-term improvements in body weight, body composition and carbohydrate, fat metabolism and emotional wellbeing.

Nor the investigated dietary additive, placebo or high-protein diet will pose any risk to general health in participants, since these are natural, commonly used dietary components and possible allergies or intolerances are established and ruled out during the screening visit. However, they might cause mild gastro-intestinal discomfort. Furthermore, adhering to a diet for 12 consecutive weeks, consisting of relatively high amounts of proteins and the investigated fibre-combination, requires motivation, compliance, time and willingness to change their normal lifestyle behaviour to a temporary lifestyle compliant with the prescribed intervention. This will subsequently pose a burden to participants, which is necessary to be able to evaluate the effects on primary and secondary outcome parameters as stated in chapter 8.

All other conducted tests will not pose a threat to the participants' health, but come with possible side-effects or complications. The physical examination, all questionnaires, collecting and providing of faecal and urine sample, neuropsychological evaluations, MRI and DEXA scan, the gut permeability test and indirect calorimetry will not harm the participants, nor pose a threat to their health. For all these tests, a participant will have to be cooperative and motivated to actively and correctly fulfil all tests and interventions, and will have to be willing to spend a vast amount of time at our facilities (40 hours in total). These tests will not pose a health risk for participants. However, the mental burden posed by these tests may be relevant. Especially the neurocognitive tests may have an impact on mental/psychological wellbeing, in particular when confronted with less optimal test results. Individual results will only be shared with the participant at their own request.

The induced radiation during a DEXA scan ( $<20 \mu\text{Sv}$ ) is far less than a Dutch citizen is exposed to on a yearly basis (2.5 mSv). This will not cause any additional health effects.

The MRI is performed in a narrow space and is known to be noisy. Some participants might experience claustrophobia, which will be examined during the screening visit, and during the scan, participants will be monitored closely.

The invasive tests (i.e. blood samples, tissue biopsies, hyperinsulinemic-euglycemic clamp) might cause more of a burden to a participant. Blood samples and intravenous cannulas will be drawn or inserted on multiple occasions, for which a sharp needle will need to penetrate skin tissue. This might hurt a participant or cause bleeding and hematoma, but is in general of minor relevance/importance/danger.

Tissue biopsies (adipose tissue and skeletal muscle) are the most invasive tests and might cause pain, hematoma, bruising or bleeding to a participant, mainly during and after the skeletal muscle biopsy. Pressure will be applied to the insertion site after the muscle biopsy to reduce the risk of hematoma and will be properly bandaged. The insertion site of both tissue biopsies will leave a small scar (~3mm for scAT and ~8mm for SMT).

During the hyperinsulinaemic-euglycemic clamp there is a small risk of hypo- or hyperglycemia. However, from our own extensive experience, these conditions do not occur very often and can be reversed immediately. A medical doctor is always available during the clamp.

Standard operating procedures (SOPs) for each measurement are available on the UM Human Biology Department's server.

